### Statistical analysis

The project will employ a mixed methods approach. Qualitative surveys for patients, multidisciplinary staff, and referrers was undertaken pre-service change to ascertain the acceptability of the digital therapy, as well as familiarity, access, confidence, and relatability of this treatment option [25]. Post-implementation surveys will also be undertaken on these same metrics. Quantitative data will be collected pre- and post-service change to ascertain treatment effectiveness in terms of clinical outcome measures, as well as service measures of interest such as patient flow, occasions of service and program engagement. Based on similar studies [40], and allowing for some incomplete data, we expect to have data for approximately 110 participants from each pre- and post- time period, resulting in a sample of 220 participants overall who will be suitable for the Direct to Psychology pathway. To assess wait times, participants will be categorised into four groups based on the time-period (pre/post implementation) and whether they met eligibility criteria for the Direct to Psychology pathway. Differences in wait times between the groups will be assessed using a one-way Analysis of Variance (ANOVA) and linear regression modelling. In a one-way ANOVA study, a sample of 220 participants, divided by 4 groups, achieves 80% power with a significance level of 0.05 to detect a moderate-large effect size (Cohen’s f) of 0.25 [41]. The effects of other variables of interest and potential confounders (patient characteristics, diagnosis,) will be tested in multivariable models. For differences in patient outcome measures pre- and post- intervention when comparing pre- and post- service change, the mean between-group difference and 95% confidence interval (CI) will be calculated. As this aspect of the evaluation is a non-inferiority trial (that is, we expect clinical outcomes to not be reduced due to the service change), the criteria adopted to determine non-inferiority will be if the upper bound 95%CI on each clinical outcome measure was less than the minimal clinical important difference (MCID). Quantitative data measuring pre- and post- service change outcomes on key indices of patient service satisfaction, service characteristics (e.g., occasions of service); as well as referrer and staff service satisfaction, and engagement with digital therapies, will be evaluated via univariate statistical tests where indicated such as independent samples t-test (or nonparametric equivalent), and categorical comparisons will be evaluated using Pearson’s chi-square. The distribution of outcome measures will be assessed, and appropriate transformations will be applied for use in modelling. Differences between group means will be tested using generalised linear regression modelling. Health related quality of life will be measured pre- and post- implementation using the EQ-5D-5 L. Population norms for EQ-5D-5 L Australia will be used to value the data set [42].

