### Intervention

#### Standard care

An exploratory qualitative analysis of consumer and stakeholder perspectives to benchmark the existing service was undertaken, followed by stakeholder consensus groups that informed the new model of care parameters including inclusion and exclusion criteria for the Direct to Psychology Pathway [24], and inclusion and exclusion criteria for assigning patients to the ‘steps’ of the stepped care model [25]. In the new Model of Care, all new referrals to the Sleep Disorders Centre will be triaged by a Sleep Physician (as per current practice) and referrals will then be directed to either Standard Care and waitlisted for a Sleep Physician initial consultation, or to the “Direct to Psychology” pathway. Note that referrals to psychology will also be accepted via the Standard Care pathway for patients requiring a medical first contact and directed to the appropriate Stepped Care treatment option.

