By incorporating consumer and stakeholder engagement throughout, we will ensure the model of care developed is acceptable to all stakeholders. By sharing and disseminating the learnings from this program to primary health services and the general community, we aim to increase engagement in evidence-based digital therapies, thus increasing the baseline sleep health of our community and reducing reliance on acute hospital services. By increasing access to, and promoting the availability of evidence-based digital therapies, we can empower consumers to engage with their own self-management, potentially reducing referrals into the acute hospital system.

Given the real-world dataset and service imperatives to be utilised, there are potential limitations to this study, including challenges in recruiting evenly to all intervention arms, and unplanned but typical participant attrition during the self-guided portion of the digital intervention, both of which may impact the results. We plan to address these challenges for those assigned to digital intervention via bi-monthly therapist or intern ‘check-in calls’ to address barriers to engagement, and to make administrative changes to triage and intake processes to flow more participants to the digital arm if indicated. However, the study is adequately powered to compensate for these factors and we anticipate that the Direct to Psychology referral pathway and Stepped Care treatment model will be acceptable to patients and clinicians and overall will improve patient care within the health system.

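### The power statement spreads 220 participants, all defined as eligible for Direct to Psychology, over four groups of which two are non-eligible, and its stated inputs give 88% power rather than 80%

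*Protocol article*

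**What the plan says.** All but one of the statements at issue are in the protocol article, Statistical analysis.

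- Numbers per period: "allowing for some incomplete data, we expect to have data for approximately 110 participants from each pre- and post- time period".
- Who these people are: the two periods together are described as "resulting in a sample of 220 participants overall who will be suitable for the Direct to Psychology pathway".
- Groups for the wait-time analysis: participants are "categorised into four groups based on the time-period (pre/post implementation) and whether they met eligibility criteria for the Direct to Psychology pathway".
- Planned test: "Differences in wait times between the groups will be assessed using a one-way Analysis of Variance (ANOVA) and linear regression modelling".
- Power: "a sample of 220 participants, divided by 4 groups, achieves 80% power with a significance level of 0.05". The effect size behind this figure is Cohen's f = 0.25, which the article labels as between moderate and large.

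Non-eligible patients are part of the study. The Standard care section notes that "referrals to psychology will also be accepted via the Standard Care pathway for patients requiring a medical first contact", and the Patients section includes all new referrals who would have reached Sleep Psychology at some point. The article gives no expected number for them.

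The Discussion names two limitations, uneven recruitment across intervention arms and attrition in the self-guided digital program, and then says that "the study is adequately powered to compensate for these factors".

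**The concern.** Two things do not fit together.

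First, the 220 are defined by eligibility, and eligibility is one of the two factors that form the groups. If all 220 are eligible, they occupy only the pre-eligible and post-eligible groups, and the non-eligible patients come on top of them. Dividing the same 220 by four contradicts the definition given shortly before.

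Second, the quoted power does not follow from the quoted inputs, even if the division by four is accepted.

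Shorter waiting time is part of the first listed hypothesis and is among the primary service access outcomes. As written, a reader cannot tell how many patients stand behind the wait-time comparison, or what difference in waiting time the study can detect. The Discussion then makes a general claim of adequate power for problems that the calculation does not address.

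**Working it through.** **Inputs.** All from Statistical analysis: N = 220, k = 4 groups, f = 0.25, alpha = 0.05, stated power 80%. About 110 participants are expected per period, after an allowance for incomplete data.

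**1. The plan's own figure.** For a one-way ANOVA, power is the probability that a noncentral F with k − 1 and N − k degrees of freedom and noncentrality N × f² exceeds the central F critical value.

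- Noncentrality: 220 × 0.25² = 13.75.
- Degrees of freedom: 3 and 216; critical value at 5%: 2.646.
- Power: **88.4%**. The stated 80% is not reproduced.

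**2. What 80% would correspond to.**

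| Change from the stated inputs | Power |
|---|---|
| N = 179, k = 4, f = 0.25 | 80.2% |
| N = 180 (45 per group), k = 4, f = 0.25 | 80.4% |
| N = 220, k = 4, f = 0.225 | 80.1% |
| N = 220, k = 4, f = 0.25, alpha 0.025 | 82.0% |
| N = 220, k = 3, f = 0.25 | 92.0% |
| N = 220, k = 2, f = 0.25 | 95.8% |

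Among the variants that keep 220 patients and f = 0.25, only alpha = 0.025 comes within two percentage points of 80%, and it contradicts the stated 0.05.

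**3. Who is in the four groups.** The text gives these expected numbers:

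| | Pre | Post |
|---|---|---|
| Eligible for Direct to Psychology | about 110 | about 110 |
| Not eligible | not stated | not stated |

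The eligible row already uses all 220. The four-group total is therefore 220 plus an unstated number. If, purely as an illustration, there were also 220 non-eligible patients (440 in equal groups), the noncentrality would be 440 × 0.25² = 27.5 and the power 99.6%. If 220 is instead the total, the eligible groups must be smaller than 110 each.

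**4. Detectable pre-post difference among eligible patients** (two-sample comparison, two-sided 5%, 80% power, in SD units of the wait-time variable as analysed). With two equal groups f = d/2, so the noncentrality is N × (d/2)².

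- 110 v 110: d = 0.379, i.e. **0.38 SD**.
- 55 v 55 (assumes that 220 is the total and is split equally): d = 0.539, i.e. **0.54 SD**.

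The two readings differ by a factor of 0.539 / 0.379 = 1.42, which is √2, as expected when the group size is halved.

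**5. The Discussion claim.** The only calculation shown is for wait time across period-by-eligibility groups. The limitations it is said to cover are imbalance between intervention arms and attrition during digital treatment. These bear on comparisons between treatment levels and on post-treatment clinical scores, and the article states no power for either.

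**The case against.** A four-group ANOVA on wait times is planned in so many words, so a reader who infers that the power statement matches no analysis in the trial goes too far. The planned test is the one being powered; what is in doubt is the group sizes put into it. Choosing an omnibus effect is also legitimate, since regression modelling is planned alongside it. Both points stand.

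The error is conservative. About 180 patients would give 80% and the plan expects 220, so the literal calculation understates the power. A reader might infer an underpowered study from the mismatch. The documents do not support that: on the wording as it stands (110 v 110 eligible) the pre-post contrast can detect 0.38 SD. Figures for a period-by-eligibility interaction would not establish a shortfall either, because the article names no such test and gives no size for the non-eligible groups.

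The 220 might be about 180 enlarged for incomplete data (180 / 220 = 0.82, an allowance of about 18%). That is possible but fits poorly, because the text presents 220 as the number with data after the allowance. It would also leave the four-group contradiction in place.

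Finally, patients are consecutive referrals within fixed dates, so the calculation does not decide who is included, and the analysis itself is unaffected. That limits the consequence to the reported sample size and power. It does not make those statements correct.

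**Conclusion.** The point holds as an inconsistency within the stated sample-size text and a power figure that cannot be reproduced. The 220 cannot be both entirely eligible and spread over four groups defined partly by eligibility. The quoted 80% should be 88.4% on the stated inputs, an understatement of 8.4 percentage points.

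The practical uncertainty is which sample the 220 describes. The detectable pre-post difference among eligible patients is 0.38 SD on one reading and 0.54 SD on the other. The second figure rests on an equal four-way split, which the article does not state. Only the sponsor can settle which reading is intended.

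The general claim of adequate power in the Discussion is not supported for arm imbalance or digital attrition, because the one calculation shown concerns wait time.

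**What to change.** In Statistical analysis:

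1. State whether 220 is the eligible subset or the whole sample.
2. Give the expected size of each of the four period-by-eligibility groups.
3. Keep the four-group ANOVA power statement, recomputed to match. If 220 is the total in equal groups, it reads 88% power for f = 0.25 at alpha 0.05. If 220 is the eligible subset, the total and the power follow once the non-eligible numbers are given.
4. Add the detectable pre-post difference in wait time among eligible patients at 80% power, two-sided 5%: 0.38 SD for 110 v 110, or 0.54 SD for 55 v 55 if that split is what is meant.

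In the Discussion, remove the sentence on adequate power, or qualify it by saying that the calculation addresses wait time and that no power is stated for the outcomes affected by uneven arms or digital attrition.

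The cost is rewording and one recalculation. No extra patients are needed and the planned analysis does not change.

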#### Direct to psychology stepped care

All patients referred to sleep psychology will complete an initial assessment according to Diagnostic and Statistical Manual (DSM-V-tr) and International Classification of Diseases (ICD-11) criteria [26, 27], including outcome measures (see *Measures).* For patients referred ‘Direct to Psychology’ additional measures will manage any potential risks associated with psychology as first contact within the model due to potential ‘missed’ medical clinical indications. These measures will include screening tools for Obstructive Sleep Apnoea (OSA) (using items from the STOP-BANG [28] and Berlin Apnoea [29] Questionnaires), hypersomnolence disorders (using items from the Cataplexy Questionnaire [30] and questions related to the presence of neuromuscular conditions, respiratory conditions and driving risk.

The inclusion criteria for Direct to Psychology criteria as defined in stakeholder co-design activities [24] include;

(i)being referred for insomnia and/or sleep psychology, and/or(ii)suboptimal adherence to OSA treatment including continuous positive airway pressure therapy (CPAP) or mandibular enhancement splint (MAS) if medical management has been already optimised.

Exclusion criteria include;

(i)significant new/changed sleep disordered breathing (or identified significant sleep disordered breathing)(ii)highly comorbid patients (e.g., neuromuscular conditions/weakness, respiratory conditions), diagnosis of hypersomnia/question of central disorder of hypersomnolence(iii)category 1 (urgent) referrals(iv)driving risk.

Patients identified as meeting the inclusion and exclusion criteria will proceed with Psychology-first intervention as indicated. Patients who meet the exclusion will be redirected back to the Standard Care model and may be re-triaged by the attending medical officer based on the additional information gleaned from the psychological assessment.

Patients progressing to psychological treatment will be matched to the appropriate treatment level. Depending on patient engagement and participation with the treatment level, as well as clinical outcomes on key assessment measures; discharge, on-referral and/or entry to another intervention level will be provided. The proposed steps of care in the new model are outlined in Fig. 2.

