*How effective was the model of care in achieving its intended outcomes?*	**Effectiveness** – impact on outcomes and quality of life/economic outcomes	**Primary outcomes** *Service Access Measures* • Average number of occasions of Service within Sleep Psychology service under ‘old’ model compared to ‘new’ model of care • Percentage of new patient activity under ‘old’ model compared to ‘new’ model of care • Average wait-time to access a first appointment with Sleep Psychology from date of referral under ‘old’ model compared to ‘new’ model of care • Average time to discharge from first appointment to final appointment with Sleep Psychology under ‘old’ model compared to ‘new’ model of care • Percentage of patients discharged from psychology *Patient-related Outcomes* • Change scores on clinical outcome measures pre- to post- treatment on clinical outcome measures (ISI, DASS-21, K10 and EQ-5D-5 L) comparing patients treated under ‘old’ model versus ‘new’ model of care • % patients treated adequately at each level of Stepped Care • Differences in patient characteristics (age, sex, geographical location, presenting issue) between those who are adequately treated at each level of the new model of care (moderation analysis) *Economic Outcomes* • Quality-adjusted life year calculations as a measure of cost-effectiveness of the ‘new’ model of care compared to the ‘old’ model of standard care **Secondary outcomes** *Patient satisfaction* • Patient satisfaction measure (SRS) post- treatment comparing patients treated under ‘old’ model versus ‘new’ model of care *Patient satisfaction with digital intervention* • Patient reported ease of access to digital intervention • Acceptability and relatability of the online program/service provided (rated by patients), including: i. motivation to access online treatment (diversion from public hospital services for insomnia treatment) ii. understanding of intervention materials iv. perceived change in sleep problem • Differences in patient characteristics (age, sex, geographical location, presenting issue) between those who complete the digital intervention compared to those who do not complete	Significantly fewer occasions of service under new model of care Significantly greater % new patient appointments under new model Significantly shorter wait-time to first appointment under new model Significantly shorter time to discharge under new model Outcomes are non-inferior under new model of care; upper bound 95%CI on outcome measures is less than MCID MCID is achieved on outcome measures by > 80% patients at each level The ‘new’ model is more cost effective Patient reported satisfaction is non-inferior under new model of care; upper bound 95%CI is less than MCID > 90% patients report positive experiences	Patient qualitative and quantitative surveys Medical Record Patient registration system

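### The wait-time hypothesis compares the new model with the old, but the only test specified and powered is an omnibus ANOVA over four period-by-eligibility groups, and no regression term is named to decide it

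*Protocol article*

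**What the plan says.** The first hypothesis under Aims and objectives is directional: waits fall under the Direct to Psychology Stepped Care Model compared with Standard Care. Table 1 (RE-AIM, Effectiveness) lists average wait to a first Sleep Psychology appointment among the primary outcomes, old model against new, with the target "Significantly shorter wait-time to first appointment under new model".

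Under Statistical analysis, "participants will be categorised into four groups based on the time-period (pre/post implementation) and whether they met eligibility criteria for the Direct to Psychology pathway". The analysis follows: "Differences in wait times between the groups will be assessed using a one-way Analysis of Variance (ANOVA) and linear regression modelling". The power statement concerns the ANOVA. It takes "a sample of 220 participants, divided by 4 groups" and claims 80% power at the 5% level for a Cohen's f of 0.25. Multivariable models are then mentioned for other variables and confounders, and generalised linear regression for differences between group means. None of these sentences says which coefficient or contrast answers the hypothesis.

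Under Direct to psychology stepped care, the features that make a patient ineligible include "category 1 (urgent) referrals", significant sleep disordered breathing, high comorbidity and driving risk.

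**The concern.** The four groups are a 2x2 layout, period by eligibility. The hypothesis concerns one part of it: the change over time in patients to whom the new pathway applies. The one-way F test asks whether any of the four means differ. It is non-directional, and it responds to a difference between eligible and ineligible patients that was present before the service change and persisted after it. Such a difference is plausible because eligibility is defined partly by triage urgency.

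At stake is how a primary service outcome is read. If the powered test is significant, readers will tend to take that as evidence on wait times under the new model, although the same result can arise when the model changed nothing. With no deciding regression term named, several candidates remain open: period overall, period within eligible patients, or the interaction.

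**Working it through.** **Inputs from the article:** 220 participants, four groups, alpha 0.05, Cohen's f = 0.25, stated power 80%. **Assumed:** equal cells of 55 (220 / 4). The article gives no cell sizes, and it describes the 220 as all suitable for the pathway, which does not sit with splitting them by eligibility. The eligibility gap in wait, d (in SD units), is also assumed and shown as a range.

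**1. The plan's own figure.** Non-centrality lambda = N f² = 220 × 0.25² = 13.75. The critical F (3, 216 df, 5%) is 2.646. Power = P(F'(3, 216, 13.75) > 2.646) = 88.4%. The stated 80% is therefore conservative for equal cells; 80% would need about 180 patients.

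**2. No effect of the model, eligibility gap d in both periods.** The cell means are 0, d, 0, d. Their SD is d/2, so f = d/2 and lambda = 220 × d²/4 = 55 d². At d = 0.5, f = 0.25, the plan's own design effect. Rejection rates of the omnibus test:

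| Gap d (SD) | lambda, 55 per cell | 55 per cell | 70:30 eligible split | 80:20 eligible split |
|---|---|---|---|---|
| 0.1 | 0.55 | 8.4% | 7.8% | 7.1% |
| 0.2 | 2.20 | 20.5% | 17.7% | 14.4% |
| 0.3 | 4.95 | 42.9% | 36.6% | 28.4% |
| 0.4 | 8.80 | 69.2% | 60.7% | 48.2% |
| 0.5 | 13.75 | 88.4% | 81.7% | 69.2% |

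A simulation of 20,000 trials at d = 0.5 with 55 per cell gave 88.4%. In every row the post-versus-pre contrast among eligible patients and the period-by-eligibility interaction each reject 5.0% of the time.

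**3. Is power lost?** Suppose the model shortens waits by 0.5 SD in the eligible post-period cell only, with 55 per cell.
- Omnibus: lambda = 55 × 0.5² × 3/4 = 10.31; power 76.7%.
- Contrast in eligible patients: 0.5 / √(2/55) = 2.62 on 216 df; power 74.2%.
- Interaction: 0.5 / √(4/55) = 1.85; power 45.5%.

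With a 70:30 split the omnibus has 85.0% and the contrast 87.0%. The two are similar.

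**4. Precision of the terms that could decide or support.** The contrast with 110 v 110 eligible patients has 80% power at about 0.38 SD and 96% at 0.5 SD. For the interaction, the difference detectable with 80% power is (1.96 + 0.84) × √(4/n): 0.76 SD at n = 55 per cell and 0.53 SD at n = 110.

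**The case against.** The strongest reply is that the ANOVA is not the whole plan. The same sentence names linear regression, and a regression on the four groups can give the period effect within eligible patients. Table 1 sets a directional old-versus-new target, which a significant F driven by eligibility would not meet. A condensed article may leave the exact coefficient to a fuller document. This stands in part: the article does not say that a significant F would be declared success, and a reader who infers that goes beyond the text. What remains is that the article itself chooses a test and powers it, that test answers a different question, and nothing ties the Table 1 target to a term in the regression.

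It is also fair to say that the rates above are power against a real eligibility difference, not type I error of the ANOVA, and that the size and direction of that difference are unknown. Urgency is only one of several exclusions.

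Two stronger readings are tempting and not supported. One is that spreading the effect over 3 df costs power; step 3 shows that it does not to any material degree. The other is that the extra screens given to Direct to Psychology patients filter the eligible post-period group in the new model's favour. No section says that status after screening defines eligibility, and Table 1 tracks eligibility, referral to the pathway and remaining on it as separate measures. Redirection follows the psychology assessment, by which time the wait to a first psychology appointment has ended. The possibility is worth closing off in wording but is not a demonstrated bias.

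**Conclusion.** The concern holds as a mismatch between hypothesis and test. A directional comparison of models is paired with a non-directional 3-df test over period and eligibility together, and the accompanying regression has no deciding term. With no effect of the model the omnibus test would be significant about 8% to 88% of the time for eligibility gaps of 0.1 to 0.5 SD. Those figures assume 55 per cell and are somewhat lower with unequal eligibility splits. A significant F therefore cannot by itself be read as a shorter wait under the new model. The finding concerns interpretation of one of several primary service measures. It does not show that the study is underpowered or that its eligibility grouping is biased.

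**What to change.** In the regression already planned, fit period, eligibility and their interaction together with the listed confounders. Name the post-versus-pre difference in wait among eligible patients as the term that decides the hypothesis, and restate the power for that contrast with the expected number of eligible patients per period. Report the period-by-eligibility interaction with its 95% CI as the check on secular trend, and label the omnibus F as descriptive only. Classify eligibility in both periods by the same rule from referral information, so that results of screens used only in the new pathway do not define the post-period group.

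The cost is a few sentences of analysis wording, a revised power statement, and applying the criteria to pre-period referral records, which the four-group split already requires. The drawback is that the main contrast is uncontrolled for secular trend and its safeguard is imprecise (step 4), so the interaction supports the main contrast and does not replace it.

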There is significant evidence for Cognitive Behaviour Therapy for insomnia (CBTi) as the first-line treatment for insomnia [2, 11], recommended by both the American Academy of Sleep Medicine (AASM) and the Australasian Sleep Association (ASA), as CBTi has extensive Level I evidence for longitudinal gains in insomnia resolution [8, 12]. Internet-delivered CBTi has been extensively investigated in the clinical literature, with systematic reviews and meta-analyses demonstrating that these first-line interventions are just as effective as face-to-face modalities in the general population for those with insomnia of low to moderate severity [6, 13–18]. “Stepped care” refers to a service delivery model allowing a relatively scarce healthcare resource to be applied in a cost-effective way to achieve timely and effective clinical care [15, 19]. CBTi is a well validated intervention with demonstrated amenability to a Stepped Care model, where patients are assessed for entry to first-line manualised and online treatment programs, increasing to progressively more time, cost and expertise intensive levels ‘upstream’ where there is an incomplete therapeutic response to a first-line intervention, or when clinical complexity demands a more intensive intervention step within the care pathway.

In our tertiary public hospital multidisciplinary sleep service, the current model of care (MoC) relies on a “medical-first” referral pathway which overburdens specialist medical services and delays care to evidence-based psychological treatment. Furthermore, intensive 1:1 interventions with the sleep psychology team results in bottlenecks in patient access. These pressures require implementation of systematised and innovative models of care, delegation to junior staff, and utilisation of time efficient (e.g., group delivery) and technological solutions designed to improve service efficiencies, effectiveness of care, and to maintain or improve patient reported experience and outcomes. A protocol for the evaluation of a new Direct to Psychology Stepped Care Model to address these pressures is presented, which utilises a direct referral pathway as well as stepped care approaches to service delivery. This study has a particular interest in exploring the feasibility and acceptability of digital intervention as a first-line treatment option.

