### Level 2: group program

The manualised CBTi intervention and sleep manual delivered during group intervention was refined by our Sleep Psychology team from an evidence-based insomnia treatment developed at Flinders University, Adelaide, Australia [32]. The intervention is 4 sessions and covers the key components of insomnia treatment – psychoeducation, sleep restriction therapy, stimulus control, cognitive therapy and relaxation training. Each session is 90 min, and there are a maximum of 6 participants in each group session. The experienced Psychologist and Intern Psychologist monitor participation and clinical outcomes during the group program.

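### The non-inferiority interval for clinical change scores, as described, makes no allowance for correlation between patients treated together in Level 2 groups; the likely effect is small and favours non-inferiority.

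*Protocol article*

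**What the plan says.** The Statistical analysis section compares pre- to post-treatment change between old-model and new-model patients: "the mean between-group difference and 95% confidence interval (CI) will be calculated". Non-inferiority on each clinical measure is accepted if the upper 95% limit is below the MCID, which implies a one-sided error of 2.5%. For group means the section adds: "Differences between group means will be tested using generalised linear regression modelling". It mentions no random effect, no cluster-robust standard error and no therapy-group identifier. It does not name the variance estimator for the non-inferiority interval either.

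On delivery, the section on Level 2 describes four 90-minute group sessions and states that "there are a maximum of 6 participants in each group session". Level 1 is self-guided digital treatment; Levels 3 and 4 are individual. On the existing service, the Background says that "intensive 1:1 interventions with the sleep psychology team results in bottlenecks in patient access", and it lists group delivery among the solutions.

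On numbers: "we expect to have data for approximately 110 participants from each pre- and post- time period". These are patients suitable for the direct pathway. The share expected to enter Level 2 is not given.

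**The concern.** Patients in one therapy group share sessions, facilitators and group process, so their change scores may be more alike than those of patients treated separately. On the article's description this arises mainly in the new model, which makes the comparison partially nested: part of one arm is clustered and the rest is not. A plain mean difference with its usual interval leaves that correlation out and understates the variance of the new-model mean.

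The direction matters more than the size. In a superiority comparison an interval that is too narrow overstates evidence of a difference. Here the decision rests on the upper limit staying below a margin, so a narrow interval helps the conclusion that the study expects to reach, and it does so for a primary clinical outcome.

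**Working it through.** **The plan's own figure.** The article gives no sample-size or power figure for the non-inferiority comparison, so there is none to reproduce on this point. Its only power statement concerns wait times (one-way ANOVA, 220 patients, four groups, f = 0.25, alpha 0.05, 80%). With those inputs a noncentral F calculation gives 88.4%. That is a separate matter and bears on nothing below.

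**Inputs from the article.** About 110 patients per period; maximum group size m = 6; 95% interval, hence a one-sided 2.5% rule.

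**Assumptions.** Share of new-model patients in groups s = 0.10 to 0.50; ICC ρ = 0.05 to 0.15; every group full; equal arms with equal standard deviation (SD); no clustering in the old-model arm.

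**Formulae.**
- A fraction s of the arm has design effect 1 + (m − 1)ρ and the rest has 1, so the variance factor of the new-model mean is D = s[1 + (m − 1)ρ] + (1 − s) = 1 + s(m − 1)ρ.
- True over unadjusted standard error of the difference, with equal arms: R = √[(1 + D)/2]. The sample size cancels.
- True one-sided error of the unadjusted limit when the true difference equals the margin: 1 − Φ(1.96/R).

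**Results for m = 6.**

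| s | ρ | D | R | One-sided error |
|---|---|---|---|---|
| 0.10 | 0.05 | 1.025 | 1.006 | 2.6% |
| 0.25 | 0.05 | 1.062 | 1.016 | 2.7% |
| 0.25 | 0.10 | 1.125 | 1.031 | 2.9% |
| 0.25 | 0.15 | 1.188 | 1.046 | 3.0% |
| 0.50 | 0.05 | 1.125 | 1.031 | 2.9% |
| 0.50 | 0.10 | 1.250 | 1.061 | 3.2% |
| 0.50 | 0.15 | 1.375 | 1.090 | 3.6% |

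The last row in full: D = 1 + 0.50 × 5 × 0.15 = 1.375; R = √(2.375/2) = 1.090; 1.96/1.090 = 1.80; 1 − Φ(1.80) = 0.036.

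So the true standard error is about 1-9% larger than the unadjusted one. Put the other way, the unadjusted one is too small by 1 − 1/R, which is 0.6% to 8.2%.

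**Interval width.** Unadjusted half-width with 110 per arm: 1.96 × √(2/110) = 0.264 SD. Over the range above it becomes 0.266 SD (0.264 × 1.006) to 0.288 SD (0.264 × 1.090).

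**Sensitivity.** With groups of four, s = 0.50 and ρ = 0.10, D = 1.15, R = 1.037 and the error is 2.9% instead of 3.2%. In the extreme case of every new-model patient in a full group with ρ = 0.10, R = 1.118 and the error is 4.0%. With s = 0 or ρ = 0 nothing changes.

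**The case against.** The strongest objection is that the article nowhere says that the clinical interval treats patients as independent. The independent-samples t-test is named for satisfaction and service measures, no variance estimator is attached to the non-inferiority interval, and an article may leave such detail to a fuller document. A reader might infer a stated independence assumption; the text does not support that. What remains is that the section does choose methods, that none of them in standard form handles clustering, and that an analyst who followed it as written would produce an unadjusted interval.

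It can also be said that one-sided clustering is an inference. It rests on the Background, and the Standard care section gives no delivery format for psychology treatment. This stands, so the claim is limited to correlation arising mainly on the new-model side. Patients may also move between levels, which would dilute a group effect, and six is a maximum rather than a typical size.

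A reader might go further and conclude that non-inferiority will be declared wrongly because of this. The figures do not support that. The error rates above apply only when the true difference sits at the margin. The article gives no numerical margin for this test, but it does quote a change above 8 points on the Insomnia Severity Index. If 8 were the margin and the SD of change were 5-8 points (both assumptions), the half-width would be about 1.3-2.1 points and the largest widening in the table would add about 0.1-0.2 points. A decision would rarely turn on that.

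Finally, a reader might extend the point to the target of more than 80% of patients reaching the MCID at each level. That target is a point benchmark with no stated interval or test, and clustering does not bias a percentage, so the point does not extend to it.

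**Conclusion.** The point holds as a minor weakness in the described analysis. The non-inferiority interval makes no visible allowance for a correlation that the new model's own group component can create, and a positive correlation would push the result towards non-inferiority. Over the assumed range the one-sided error is about 2.6-3.6% instead of the intended 2.5%. The size depends on two quantities that the article does not give, the Level 2 share and the ICC, and on full groups of six; smaller groups or a smaller share bring it closer to nothing. It is worth correcting because the direction favours the study's hypothesis and the correction is cheap, not because it threatens the conclusion.

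**What to change.** Record the Level 2 therapy-group identifier at data extraction. Compute the non-inferiority interval from the planned regression with standard errors clustered on therapy group, each other patient forming a cluster of one, and with a small-sample correction.

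A partially nested mixed model (random effect for therapy group among Level 2 patients only) is an alternative if there are enough groups to estimate it. There may not be: with 25% of 110 patients in groups of six there are about 27.5/6, or roughly five, groups; with 50%, about 55/6, or nine. A group variance estimated from so few would be unstable, so the clustered standard error is the safer default, and the small-sample correction should not be left out.

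The cost is one extra data field, one sentence in the analysis section and a slightly wider interval. No treatment or visit changes.
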